### Sample Size

The target sample size for the population survey and learning systems sample is 2000. This sample size will also allow for the estimation of the impact of the dashboard and app recommendations on score trajectories of the PHQ-9 and 7-item Generalized Anxiety Disorder Scale (GAD-7). Based on an estimated effect size of Cohen *d*=0.17 for changes in the PHQ-9 score and Cohen *d*=0.13 for changes in the GAD-7 score (based on the expected effects of the dashboard) [15], an expected dropout rate of no more than 35% [16], and population mean and SD estimates of PHQ-9 and GAD-7 scores [17,18], we estimate having a power of 0.90 and a type I error rate of 0.05 for detecting improvements in PHQ-9 and GAD-7 scores for subsamples with at least 1000 participants. Therefore, in this study, we will have a sample size of a total 2000 participants, with 1000 randomized to each group.

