This study aims to evaluate the effectiveness and cost-effectiveness of the WTC portal by conducting a randomized controlled trial. The control group will be referred to the usual care tools available on the CAMH (Centre for Addiction and Mental Health) website. CAMH provides a range of self-care interventions, particularly different mental health programs and resources such as “Game Changers: Self-care information,” which is a hub of resources to help start a conversation about health, including a self-help booklet series, a relaxation guide, and free web-based education with a personalized dashboard, which provides an opportunity for the client to self-monitor (symptoms or physiological processes), build awareness, and improve self-efficacy and visualization. Usual care tools such as digital interventions have a self-care and self-help component. Many studies have shown positive outcomes deemed acceptable and feasible with >95% completion rates and a high degree of participation with self-care interventions; some offer significant early benefits of tailored self-care programs [12,13]. A meta-analysis indicates that these interventions can be effective and potentially be future home-based interventions, especially in mental health care such as digital interventions; hence, it has been chosen as a control intervention in this study.

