### Blinding

Both participants and the research team involved in the trial will be blinded about the groups. The groups will be observed in an identical manner by the study team to ensure randomization. Further, to ensure that the study team is double-blinded, the potential participant receiving the intervention or usual care will be contacted by a research assistant outside the research team. The 2 groups will be followed up for 26 weeks to determine whether there are any differences in outcomes between them. The results and subsequent analysis of the trial will be used to assess the effectiveness of the WTC portal, which is the extent to which the service benefits the patients rather than doing them any harm.

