### Control

The control group will be referred to the usual care tools available on the CAMH website, particularly (different mental health programs and resources such as “Game Changers: Self-care information,” which is a hub of resources to help start conversations about health, self-help booklet series, relaxation guides, and free web-based education with a personalized dashboard), which provides an opportunity to clients for self-monitoring (symptoms or physiological processes), build awareness, improve self-efficacy, and visualization. The control group will not receive process monitoring assessments at week 6 or 26. Service usage and contamination in the control group will not be monitored.

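### The power statement rests on an expected dashboard effect, but the trial randomises WTC against CAMH self-care tools: the randomised contrast cannot isolate a dashboard effect, and the 0.90 power is not tied to it

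*Protocol article*

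**What the plan says.** The Sample Size section of the protocol article gives the sample a purpose: "This sample size will also allow for the estimation of the impact of the dashboard and app recommendations on score trajectories". It plans on "Cohen *d*=0.17 for changes in the PHQ-9 score" and "Cohen *d*=0.13 for changes in the GAD-7 score", and gives their origin as "based on the expected effects of the dashboard". With dropout of up to 35%, it concludes: "we estimate having a power of 0.90 and a type I error rate of 0.05". The power is said to apply to subsamples of at least 1000, and the section ends with 2000 participants, 1000 per group. No other effect size is offered in support of that number.

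The randomised comparison is a different one. Trial Design asks how effective WTC is compared with usual care, primarily for anxiety. The Control section defines usual care as tools on the CAMH website, including "free web-based education with a personalized dashboard), which provides an opportunity to clients for self-monitoring (symptoms or physiological processes". The Introduction explains the choice of comparator: "A meta-analysis indicates that these interventions can be effective and potentially be future home-based interventions". Statistical Analysis plans an intention-to-treat analysis with linear random effects models that compares trajectories between the two groups. The Blinding section gives the purpose of the results: "assess the effectiveness of the WTC portal, which is the extent to which the service benefits the patients rather than doing them any harm".

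**The concern.** A power statement is useful only if its effect size belongs to the comparison being tested. Here the effect size belongs to a dashboard, while the test compares two packages of digital services. The article gives no expected difference between WTC and the CAMH tools, so a reader cannot tell what the trial is powered to detect on its primary trajectory, anxiety.

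The section also promises an estimate that the randomisation does not provide, because no one is allocated to dashboard or no dashboard. Two things are at stake. A dashboard effect might be reported as if it had randomised support. A non-significant WTC result might be read against a 90% power that was never shown for that contrast.

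**Working it through.** **Step 1. Can the randomised contrast isolate a dashboard effect?**

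The control arm's dashboard is documented (Introduction and Control). For WTC, the Introduction lists self-monitoring tools among many components, and neither it nor the Intervention section names a dashboard. There are two cases:
- If WTC has a comparable dashboard, the feature is common to both arms and largely cancels.
- If it does not, the dashboard sits on the control side and is confounded with everything else that differs between the packages.

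In neither case does WTC minus CAMH equal a dashboard effect.

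**Step 2. Reproduce the stated 0.90.**

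Inputs from Sample Size: d = 0.13 and 0.17, α = 0.05 (sidedness not stated), 1000 per arm, dropout up to 35%, so 1000 × (1 − 0.35) = 650 per arm. Assumptions: outcome SD standardised to 1, normal approximation.

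Two-arm power = Φ(d·√(n/2) − z), with z = 1.960 two-sided or 1.645 one-sided.

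For GAD-7, two-sided, n = 650: 0.13 × √325 = 2.344, and Φ(2.344 − 1.960) = Φ(0.384) = 0.65.
For PHQ-9, two-sided, n = 650: 0.17 × √325 = 3.065, and Φ(1.105) = 0.87.

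| Two-arm test, unadjusted | GAD-7, d=0.13 | PHQ-9, d=0.17 |
|---|---|---|
| Two-sided, 650 per arm | 0.65 | 0.87 |
| Two-sided, 1000 per arm (no dropout) | 0.83 | 0.97 |
| One-sided, 650 per arm | 0.76 | 0.92 |
| One-sided, 1000 per arm (no dropout) | 0.90 | 0.98 |

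**Step 3. What else gives about 0.90 for GAD-7?**

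- One-sample within-person test, two-sided, 650 remaining in one group: Φ(0.13 × √650 − 1.960) = Φ(1.354) = 0.91. This uses the stated inputs with dropout and no added correlation, but it is not a between-arm test.
- Baseline-adjusted two-arm test, two-sided, 650 per arm, SD multiplied by √(1 − r²). The correlation r is not given, so it is shown as a range: 0.69 at r = 0.3, 0.77 at r = 0.5, 0.83 at r = 0.6, 0.91 at r = 0.7.
- Combinations also work. One-sided with r = 0.6 and 650 per arm gives Φ(2.344/0.8 − 1.645) = Φ(1.285) = 0.90.

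The article does not say which of these, if any, was used.

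**Step 4. What the two-arm test can detect.**

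Two-sided, 650 per arm, unadjusted:
- Detectable d at 90% power = (1.960 + 1.282) × √(2/650) = 3.242 × 0.0555 = 0.18.
- Half-width of the 95% confidence interval = 1.960 × 0.0555 = 0.11 SD.
- For 90% power at d = 0.13: 2 × 3.242² / 0.13² gives 1244 per arm analysed, and 1244/0.65 gives 1914 per arm randomised. At d = 0.17 the figures are 728 and 1120.

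**Step 5. Sensitivity to the unknown WTC-versus-CAMH effect.**

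The article gives no such effect. As an illustration only, with 650 per arm, two-sided and unadjusted:

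| Between-arm effect as a share of the dashboard d | GAD-7 | PHQ-9 |
|---|---|---|
| 100% | 0.65 | 0.87 |
| 75% | 0.42 | 0.63 |
| 50% | 0.22 | 0.33 |
| 25% | 0.08 | 0.12 |

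The true difference could also exceed the dashboard effect, since WTC offers coached programs and counselling.

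**The case against.** The best defence is that the dashboard is an extra use of the sample. The quoted sentence says it will also allow that estimate, and the article plans within-person modelling (Primary Outcomes, Statistical Analysis), through which a dashboard effect might be sought. The within-person calculation even lands near 0.90. This stands as far as it goes, but such an estimate would be non-randomised. The section still moves from dashboard effect sizes to 1000 randomised per group without giving any effect for that comparison.

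A second defence is that repeated measures and baseline adjustment raise power above the unadjusted 0.65, and that participants who drop out still contribute earlier data. That is also fair. The unadjusted figure is a reference point, not a prediction, but the article states no correlation that would support 0.90.

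Three stronger readings are tempting and should be resisted:
- A reader might infer that both arms have a dashboard. Only the CAMH one is documented, and the article does not say that it is the dashboard meant in Sample Size.
- A reader might infer that a null result would say nothing about WTC. The first research question is effectiveness compared with usual care. The randomised contrast estimates exactly that, to within about ±0.11 SD. It would not address WTC against no intervention.
- A reader might infer that the Blinding section would treat a null as showing WTC to be ineffective. It does not say so, and its preceding sentence speaks of differences between the groups. Its gloss on effectiveness is loose because it does not name the comparator.

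An active comparator is a legitimate choice, and the article already calls the trial alternative intervention–controlled.

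**Conclusion.** The point holds in this limited form. The sample size is justified only by effect sizes attributed to a dashboard. The randomised comparison is WTC versus CAMH tools that include a personalised dashboard, so it cannot isolate a dashboard effect, whether or not WTC has one. The 0.90 is not shown for the trial's own contrast: on the article's inputs, the two-arm, two-sided, unadjusted calculation gives about 0.65 for GAD-7 and 0.87 for PHQ-9.

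These figures assume a standardised SD of 1, the full 35% dropout and no gain from baseline or repeated measures. With such gains the power could be higher, and with a smaller between-arm effect it would be lower. The randomised comparison itself remains valid for the question of WTC relative to the CAMH tools. What needs correcting is the claim about the dashboard and the basis of the power.

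**What to change.** 1. In Sample Size, delete the claim about the impact of the dashboard and app recommendations, or label it as a non-randomised within-person analysis.
2. State that the power calculation concerns WTC versus CAMH digital self-care tools. Either justify d=0.13 and d=0.17 for that contrast or say plainly that they are borrowed from a different one. Merely relabelling them as a difference between two active services would remove their only stated basis and supply no other.
3. Restate the power for the two-arm test, giving sidedness, dropout and any assumed correlation. Alternatively, state the detectable difference: about d=0.18 at 90% power, two-sided, 650 per arm, no baseline adjustment.
4. In Blinding, describe the result as the effectiveness of WTC relative to the CAMH tools, not relative to no intervention.

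The cost is a text change and a short recalculation, with no change to randomisation or data collection. The downside is a narrower claim and, unless an adjustment is justified, a less favourable stated power for anxiety.

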## Methods

### Trial Design

The Let’s Act on Mental Health study is a longitudinal, fully remote, equally randomized (1:1), double-blind, alternative intervention–controlled, parallel-group randomized controlled trial to be conducted between October 2023 and April 2024 with a prospective follow-up for 26 weeks. This trial will evaluate whether digital interventions such as WTC improve population mental health trajectories over time. The trial will consist of 1 baseline assessment at week 0, 13 biweekly short and long follow-ups from week 24, intervention monitoring twice at weeks 6 and 26, and 1 final assessment at the end of the 26-week follow-up period. An overview of the trial process is shown in Figure 1.

The study’s overall objective is to evaluate the effectiveness and cost-effectiveness of the WTC portal by conducting a randomized controlled trial. We will use a “Knowledge-to-Action Framework” [14] with extensive stakeholder and cross-sectoral engagement and will incorporate program elements with people with lived experience.

The research questions we seek to answer with this study are the following: (1) how effective is the WTC portal in altering the trajectories of mental health and substance use, primarily anxiety, compared to usual care? (2) What is the benefit of WTC versus usual care in terms of incremental costs, health outcomes, ongoing recruitment, and maintenance costs compared to the cost per quality-adjusted life year (QALY) gained using these interventions? (3) What is the differential impact of WTC by age, sex or gender, race, and socioeconomic status?

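### The stated 0.90 power is not delivered for the randomised GAD-7 comparison: on the article's own inputs, two-sided unadjusted between-arm power is about 0.65

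*Protocol article*

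**What the plan says.** The Sample Size section gives d=0.17 for PHQ-9 change and d=0.13 for GAD-7 change. It attributes both to a dashboard, cites population means and SDs without printing them, and allows for dropout of up to 35%. It then says "we estimate having a power of 0.90 and a type I error rate of 0.05 for detecting improvements in PHQ-9 and GAD-7 scores" and continues "for subsamples with at least 1000 participants. Therefore, in this study, we will have a sample size of a total 2000 participants", split 1000 to each group. It names no test, no sidedness and no within-person correlation.

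The Trial Design section makes the first research question comparative: "how effective is the WTC portal in altering the trajectories of mental health and substance use, primarily anxiety, compared to usual care". Primary Outcomes and Statistical Analysis both set the intervention trajectory against that of the control group. Statistical Analysis names change in anxiety from baseline to week 26 as the primary trajectory. GAD-7, which has the smaller effect size, therefore governs the sample size.

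**The concern.** The power is claimed for one subsample of 1000, and the total is then reached by having two such groups. That reasoning fits a test of change within one group. A between-arm difference with n per arm has a standard error √2 times that of a one-group mean change on n people, so the same d gives less power. A reader would take the risk of missing the anxiety effect as 10%, when the stated inputs do not support that for the randomised comparison. The power figure is the only justification offered for 2000 participants, and it bears on how a null result would be read.

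**Working it through.** **Inputs from the Sample Size section.** d=0.13 (GAD-7), d=0.17 (PHQ-9), alpha 0.05, dropout 35%, 1000 per arm. Completers per arm: 1000 × 0.65 = 650. Sidedness is not stated; two-sided is assumed (z=1.960) and one-sided is also tried (z=1.645). SD is set to 1 because the effects are standardised.

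**Reproducing the stated figure.** One-group test of change, power = Φ(d√n − z):
- GAD-7, n=650: 0.13 × √650 = 3.314; 3.314 − 1.960 = 1.354; power 0.912 (0.911 with the noncentral t).
- In reverse, 0.90 power needs (1.960 + 1.2816)²/0.13² = 622 completers, and 622/0.65 = 957 enrolled, close to the 1000 in the text.

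This route uses every stated input and lands near 0.90.

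**Between-arm comparison.** Power = Φ(d√(n/2) − z), n per arm, with d read as the standardised between-arm difference in change:

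| GAD-7, d=0.13 | d√(n/2) | Two-sided power | One-sided power |
|---|---|---|---|
| 650 per arm (35% loss) | 2.344 | 0.649 | 0.758 |
| 1000 per arm (no loss) | 2.907 | 0.828 | 0.897 |

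For PHQ-9, d=0.17 at 650 per arm gives 0.865 two-sided.

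**Smallest d with 0.90 power at 650 per arm.** (1.960 + 1.2816) × √(2/650) = 0.180.

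**N needed for 0.90 at d=0.13, unadjusted.** 2 × 3.2415²/0.13² = 1244 completers per arm; 1244/0.65 = 1914 randomised per arm; 3828 in total.

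**If d is on the raw-score SD scale and baseline is adjusted for.** Replace d by d/√(1 − r²), where r is the baseline to week 26 correlation. The article does not state r, so these values are assumptions. At 650 per arm, two-sided:
- r=0.5: 0.13/0.866 = 0.150, power 0.77
- r=0.6: 0.13/0.800 = 0.163, power 0.83
- r=0.7: 0.13/0.714 = 0.182, power 0.91

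**The case against.** The strongest reply is that 0.65 is one point in a range.
- The mention of population SDs suggests that d may be on the raw-score scale. Baseline adjustment could then bring power to 0.90, but only at r of about 0.7. On that same scale an unadjusted comparison of change scores gives 0.51 at r=0.3, 0.65 at r=0.5 and 0.86 at r=0.7 (all assumed), so the unknown correlation cuts both ways.
- The planned random effects model uses partial data from people who drop out, so 650 completers is a simplification. This stands. Yet for unadjusted change from baseline to week 26, complete data on all 2000 still give only 0.83.
- A contrast that averaged all follow-ups could exceed 0.90 under an assumed exchangeable correlation of 0.5. The article names change over weeks 0 to 26 as primary and claims no such gain.
- A one-sided test comes to 0.897, but only if the stated dropout is ignored; with it, the figure is 0.76.

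Three stronger readings are tempting and are not supported:
- *The authors ran a one-group pre-post test.* No test is named. The wording and the match to 0.91 point that way, but it remains an inference, and the shortfall does not depend on it.
- *The trial has a 35% risk of missing its primary effect.* That holds only if d=0.13 is the between-arm difference in change. The article does not say so; if it is not, between-arm power is simply not established.
- *The effect size is invalid because controls also get a dashboard.* The Control section does list "free web-based education with a personalized dashboard", but nothing shows that this is the tool behind the effect sizes, and the cited source is not at hand.

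**Conclusion.** The point holds in conditional form. The Sample Size section does not show 0.90 power for the randomised GAD-7 comparison. With d=0.13 read as the standardised between-arm difference in change, two-sided alpha 0.05 and 35% loss, unadjusted power is about 0.65. Neither assuming no loss (0.83) nor testing one-sided with the stated loss (0.76) restores 0.90. Baseline adjustment does so only with d on the raw-score scale and r of about 0.7, neither of which is stated. The problem is mainly with anxiety; the PHQ-9 shortfall is small (0.865 against 0.90). The PHQ-9 figure has a separate difficulty: Table 1 schedules PHQ-4 at baseline, follow-up and final assessment, and lists PHQ-9 only as item 9 at screening.

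**What to change.** Keep N=2000 and rewrite the paragraph for the between-arm GAD-7 comparison, naming the test, sidedness, the scale of d and any assumed correlation. For example:

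> With 1000 per arm and 35% loss, two-sided unadjusted power is about 0.65 for d=0.13; 0.90 power is reached for d=0.18; with adjustment for baseline GAD-7, power is X under r=Y.

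Then:
- Make the stated power match the primary model that will actually be used. If baseline adjustment is cited, it has to be in that model.
- Delete the clause that ties power to subsamples of 1000.
- State whether d=0.13, which the article attributes to a dashboard, is meant as a portal-versus-control difference.
- Give a depression power figure (0.87 for d=0.17, unadjusted) only if PHQ-9 is collected at follow-up. Reconcile the Sample Size section with Table 1 on this.

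The cost is a less favourable stated power and some rewording. No extra participants are needed. If baseline adjustment is not already part of the primary model, adding it is a change to the analysis and should be declared as one.

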### Randomization

At week 1, after baseline assessments, participants will be randomly allocated through email invitation to intervention or control groups using a simple randomization method equivalent of tossing a coin to ensure double-blinding. Participants deemed eligible after a manual-fraud check will be emailed a personalized URL invitation based on the groups in the study by the research personnel within the study, using the email template attached.

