### Statistical Analysis

A statistician who is not affiliated with this study will perform the statistical analyses for Linear random effects modeling—which accounts for repeated measures over time—that will be used to study the intervention’s effect [24]. We will also use multilevel modeling to describe within-person differences in anxiety and depression. We will then compare this observed trajectory with the control group’s trajectories.

The level of change in anxiety from weeks 0-26 (baseline to final assessment) over the 6 months’ time period is the primary trajectory of concern for mental health in this study. We will test the hypothesis that the trajectories are changing over time and the intervention’s effects are expected to be observed as changes in self-reported mood, which will be measured with the mood scores, cutoff scores, sensitivity, etc, obtained at various time points. Interactions by demographic subgroups (primarily age, gender, race, and socioeconomic status) will be assessed for identifying potential effect modifications.

Analysis will be based on the intention-to-treat principle, as this method allows to draw an unbiased conclusion regarding the effectiveness of an intervention. It also preserves the benefits of randomization, which cannot be assumed when using other methods of analysis [25]. Further, this method is also more effective in accommodating missing data, as missingness is assumed at random.

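### The primary GAD-7 contrast is worded as change from week 0 to week 26; stating baseline adjustment would gain precision from data already collected

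*Protocol article*

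**What the plan says.** The Randomization section of the protocol article describes a "simple randomization method equivalent of tossing a coin", carried out at week 1 once baseline assessments are complete. It names no stratification factor. Table 1 places GAD-7 at week 0, so every participant's baseline anxiety score is known before allocation.

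The Statistical Analysis section identifies the primary trajectory by the words "The level of change in anxiety from weeks 0-26 (baseline to final assessment", over six months. The Primary Outcomes section also frames the outcome as change from week 0 to week 26. The model is a linear random effects model for repeated measures, and the intervention trajectory is compared with that of the control group. Neither section names baseline GAD-7 as a covariate or says whether the arms share a week-0 mean.

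The Sample Size section is also set on change: "Cohen *d*=0.13 for changes in the GAD-7 score", with "a power of 0.90 and a type I error rate of 0.05" and dropout of up to 35%, leading to a "sample size of a total 2000 participants, with 1000 randomized to each group".

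**The concern.** When baseline is measured before randomisation, the difference between arms in change and the baseline-adjusted difference at week 26 estimate the same treatment effect. They differ in precision. The change contrast gives the baseline score a weight of exactly 1, while the best weight is the baseline to week 26 correlation, which is normally below 1. The excess weight adds variance.

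In a random effects model, this depends on the mean structure. With terms for arm, time and arm by time, the week-0 means are free to differ and the arm-by-time contrast is a change contrast. If the arms share a week-0 mean, the model makes the baseline adjustment itself. The article's wording points to the former and does not state the latter.

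This matters more than usual here because the effect sought is only 0.13 SD. An analysis plan that follows the article's wording literally would give up precision that costs nothing to keep.

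**Working it through.** **Inputs from the protocol article.** Effect 0.13 for GAD-7 change (the standardising SD is not given); alpha 0.05 (sidedness not given); 1000 per arm; 35% dropout, hence 1000 × 0.65 = 650 completers per arm; 14 assessments (Duration and Assessments section).

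**Assumed.** Baseline to week 26 correlation r of 0.5 to 0.7; equal variance at both times; for the slope calculation, equally spaced visits and equal correlation between all visits.

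**1. The stated power.** Power = Φ(d × √(n/2) − z).
- Two-sided, 1000 per arm: Φ(0.13 × √500 − 1.96) = Φ(0.947) = 0.83.
- Two-sided, 650 per arm: Φ(0.13 × √325 − 1.96) = Φ(0.384) = 0.65.
- One-sided, 1000 per arm: Φ(2.907 − 1.645) = 0.90, which ignores dropout.
- One-sided, 650 per arm: 0.76.
- Within-person test in a single group of 650, two-sided: Φ(0.13 × √650 − 1.96) = 0.91, which is not the between-arm contrast.

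The stated 0.90 is therefore not reproduced for a two-sided comparison between arms after dropout. The starting point below is 0.65.

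**2. Variance of the two contrasts.** In units of the raw GAD-7 variance per participant, the change score has variance 2(1 − r) and the baseline-adjusted score 1 − r². Their ratio, adjusted to change, is (1 + r)/2.

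| r | Ratio | Variance saved |
|---|---|---|
| 0.5 | 0.75 | 25% |
| 0.6 | 0.80 | 20% |
| 0.7 | 0.85 | 15% |

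A generalised least squares calculation with 14 visits and time as categories gives the same ratios at r = 0.5 and 0.7 for the week 26 contrast, comparing free with equal week-0 means. If a linear slope is tested instead, the ratios are 0.852 (r = 0.5) and 0.928 (r = 0.7), so the saving is about 15% to 7%.

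**3. Power after adjustment, 0.13 taken on the change-score SD.** The effective standardised effect is 0.13/√((1 + r)/2).
- r = 0.5: 0.150, power at 650 per arm 0.77.
- r = 0.6: 0.145, power 0.75.
- r = 0.7: 0.141, power 0.72.

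Completers needed per arm for 0.90 two-sided: 2 × (1.96 + 1.2816)²/0.13² = 1244 with the change contrast, falling to 933 (r = 0.5) or 1057 (r = 0.7).

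**4. If 0.13 is on the raw GAD-7 SD instead.** Change versus adjusted power at 650 per arm is 0.65 versus 0.77 (r = 0.5), 0.75 versus 0.83 (r = 0.6) and 0.86 versus 0.91 (r = 0.7). Adjustment gains on either scale. The shortfall against 0.90 depends on which scale was meant.

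**5. Allocation.** A coin toss over 2000 gives an arm size with SD √2000/2 = 22.4, so about 956 to 1044 in 95% of cases. The efficiency at that limit is 4 × 956 × 1044/2000² = 0.998, a loss of about 0.2%.

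**The case against.** A separate analysis plan may exist, and covariate lists and mean structures are commonly left to it. A model with a common week-0 mean is itself a linear random effects model, so the article does not rule it out, and if that is what is planned the gain is already secured. This stands, and it is why silence about covariates is not the point here. The point is that the article does fix the contrast as change from week 0, and a better contrast is available with the same data.

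A reader might infer more: that baseline GAD-7 goes unused, that chance imbalance stays uncorrected, or that the coin toss is at fault. The documents do not support these readings.
- Change from week 0, and a trajectory starting there, both use the baseline score.
- A baseline gap is subtracted in full. What remains is regression to the mean, (1 − r) times the gap in the opposite direction. With 1000 per arm, the 95% limit of the gap is 1.96 × √(2/1000) = 0.088 SD, leaving 0.026 to 0.044 SD for r of 0.7 to 0.5. At one standard error (0.045 SD), it leaves 0.013 to 0.022 SD.
- Under randomisation the estimate is unbiased, and its standard error already includes chance imbalance. That residual shift and the extra variance are one cost, not two.
- Unstratified allocation loses almost nothing at this size.

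**Conclusion.** The point holds as one of precision. As worded, the primary contrast is valid and unbiased but less efficient than the collected data allow. For r between 0.5 and 0.7, the avoidable variance is 25% to 15% for a week 26 contrast and about 15% to 7% for a linear slope. On the change-score reading of 0.13, two-sided power with 650 completers per arm moves from about 0.65 to 0.77–0.72. Adjustment therefore recovers part of the gap to 0.90 and does not close it; the stated power is a separate question about the Sample Size section.

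The size rests on an r that the article does not give, on two-sided testing, and on counting completers only, although the model would also draw on partial follow-up. The gain is nil if the model already holds week-0 means equal.

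**What to change.** In the Statistical Analysis section, define the primary effect as the between-arm difference in GAD-7 at week 26 estimated from the longitudinal model, either with week-0 means constrained equal across arms or with baseline GAD-7 as a covariate, and name which. The equal-mean constraint is justified by design, because GAD-7 is measured before allocation. Align the wording in the Primary Outcomes section. If a slope is intended as the primary test, say so and apply the same constraint.

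The cost is one sentence. No new data or participants are needed and allocation stays as it is. The Results section reports that follow-up data are already being analysed, so the choice should be fixed and dated before any comparison between arms.
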